### Cardiac reserve

Cardiac reserve will be quantified using exCMR. The real-time CMR protocol used in this study has been described in detail previously and validated against invasive measures [33]. In brief, imaging will be performed with a Siemens MAGNETOM Prisma 3.0 T CMR with a 5-element phased array coil. Ungated real-time steady state free-precision cine imaging will be performed without cardiac or respiratory gating. Using this technique, our group has demonstrated excellent interobserver (R = 0.98 and R = 0.97 for LV and RV SV, respectively) and interstudy reproducibility (R-0.98 for Qc) [33].

After resting images have been obtained, subjects will cycle on an ergometer compatible for magnetic resonance imaging ([MRI]; MR Ergometer Pedal, Lode, Groningen, Netherlands – Fig. 3) at an intensity equal to 20, 40 and 60% of maximal power output obtained during the upright incremental CPET. These workloads will subsequently be referred to as rest and low, moderate, and high intensity. It has been previously determined that 66% of the maximal power during upright cycling approximates maximal exercise capacity in a supine position for non-athletes [49, 50]. Each stage of exercise is maintained for up to 1.5–3 min; approximately 30 s to achieve a physiological steady-state and 1–2.5 min for image acquisition.

**Fig. 3 Fig3:**
[figure not shown]
Exercise is performed within the MRI scanner (top image) using the Lode MR Ergometer Pedal with images acquired in real-time during exercise. Exercise is performed at workloads individualised from each participant’s peak workload from their upright cardiopulmonary exercise test

**Fig. 4 Fig4:**
[figure not shown]
Example of real-time ungated exercise cardiac MRI imaging during high-intensity exercise. **a** Short axis images are used to define the endocardial borders for the calculation of ventricular volumes. The point at which these transect the horizontal long-axis plane (**b**) is shown by the pink dots at the line of the red dotted line. This allows for cross-checking for the accuracy of endocardial contours and for the determination of the atrio-ventricular level on the short axis images. The endocardial ventricular borders for each short-axis slice at (**c**) end-diastole and (**d**) end-systole are summed to determine end-diastolic and end-systolic ventricular volumes respectively. This process is performed for images taken at rest and all intensities of exercise

Images will be analysed on a software program developed in-house (RightVol – Right Volume Leuven, Leuven, Belgium) in which the physiological data (respiratory movement and ECG) are synchronized to the images so that contouring can be performed at the same point in the respiratory cycle thereby greatly minimizing cardiac translation error Fig. 4. Left ventricular (LV) and right ventricular (RV) endocardial contours will then be manually traced on the short axis image, and the points of transection with the horizontal long axis plane are indicated, thus enabling constant referencing of the atrioventricular valve plane. Trabeculations and papillary muscle will be considered part of the ventricular blood pools and volumes will be calculated by a summation of disks (Fig. 3). SV will be calculated from the difference between end-diastolic volume and end-systolic volumes, while Qc will be calculated as (RVSV+LVSV/2) × HR. Peripheral muscle arterio-venous oxygen extraction will be estimated according to the Fick principle [51], using V̇O_2_peak measured by CPET and peak Qc measured by exercise CMR with adjustment for changes in haemoglobin concentration. Cardiac reserve will be defined as the change in Qc from rest to the high intensity workload. This study will also assess changes in HR, SV, LVEF and RVEF at each stage of exercise (rest, low, moderate and high intensity workloads) as additional measures of cardiac reserve.

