### Primary and secondary outcome measures

The primary outcome for this study will be the prevalence of functional disability (defined as VO_2_peak ≤ 18.0 mL/kg/min) measured via CPET at 12 months. The predictive ability of standard-of-care versus novel cardiac reserve measures will be addressed by comparing LVEF assessed via 3-dimensional (3D) echocardiography to cardiac reserve assessed via exCMR. For the purposes of this study, impaired cardiac reserve will be defined as a < two-fold increase in Qc from rest to peak exercise [33]. Impaired LVEF will be defined as a LVEF < 53% which is in line with current cardio-oncology guidelines [14, 15, 17].

Secondary outcomes will include changes in cardiopulmonary fitness and cardiac reserve, along with indices of resting cardiac structure and function, vascular stiffness, biochemical and blood-based markers of cardiovascular function, total- and regional body composition, bone mineral density of the lumbar spine and femoral neck, muscle strength, physical function, habitual physical activity, cognitive function, and multidimensional quality of life.

Additional exploratory outcomes will include the association between changes in cardiopulmonary fitness with indices of cardiac (cardiac reserve) versus non-cardiac factors (central vascular stiffness, haemoglobin concentration, lower body lean body mass, skeletal muscle composition of the thigh). The study will also explore the effect of the intervention on treatment-related variables including the dose of treatment received and response to neoadjuvant therapy.

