#### Rey auditory verbal learning test

Changes in verbal memory and learning will be assessed using the Rey Auditory Verbal Learning Test [63]. Outcomes include the total number of words correctly recalled on each attempt, the number correctly recalled after interference, loss after interference (trial 5 minus trial 2) and correct recall after the extended delay period.

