The second primary aim of the study is to compare the predictive ability of standard-of-care measures (LVEF) with peak Qc measured by ExCMR in identifying women who will meet criteria for functional disability at 12 months. A multivariate regression will be used with five variables entered (age, LVEF, GLS, study group and peak Qc). The analysis will be stratified for group allocation (usual care vs exercise training) to account for the potential influence of the exercise intervention on the incidence of functional disability at 12-months. The sample size estimated for such an analysis can be calculated as 90 women (50 + 8 x no. of variables) using the method suggested by Green [74].

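### Two outcome formulas are wrong as printed: cardiac output halves only one ventricle's stroke volume, and the verbal-memory loss score leaves out the post-interference recall

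*Protocol article*

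**What the plan says.** **Cardiac output.** The Cardiac reserve section of the protocol article (text after the Fig. 4 caption) first defines stroke volume: "SV will be calculated from the difference between end-diastolic volume and end-systolic volumes". It then states: "Qc will be calculated as (RVSV+LVSV/2) × HR". The same paragraph uses peak Qc with VO2peak in a Fick estimate of oxygen extraction, and adds: "Cardiac reserve will be defined as the change in Qc from rest to the high intensity workload".

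**Where Qc is used.** The section on sample size and statistical analysis says that the second primary aim is to "compare the predictive ability of standard-of-care measures (LVEF) with peak Qc measured by ExCMR". It specifies the model: "A multivariate regression will be used with five variables entered (age, LVEF, GLS, study group and peak Qc"). Under Primary and secondary outcome measures, "impaired cardiac reserve will be defined as a < two-fold increase in Qc from rest to peak exercise".

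**Verbal memory.** The Rey auditory verbal learning test section lists the words recalled on each attempt, the number recalled after interference, "loss after interference (trial 5 minus trial 2"), and recall after the extended delay.

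No other part of the article restates or corrects either formula.

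**The concern.** Dividing by two makes sense here only as an average of the two ventricles. By ordinary operator order, the printed expression instead adds the whole right ventricular stroke volume to half of the left. Qc is the imaging measure set against LVEF in a primary aim. It also underlies cardiac reserve in L/min and is the denominator of the Fick estimate, so anyone who programs the printed line carries the error into all of these.

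The memory score has a different fault. A loss after interference has to compare recall before the interference with recall after it. The printed difference contains no post-interference term, although that recall is collected. Read as numbered attempts in order, it grows as a participant improves, so a better learner would be recorded as having lost more.

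**Working it through.** The plan gives no numerical result for either formula, so there is no stated figure to reproduce. The check is algebra plus worked examples. The stroke volumes, heart rates, word scores and RVSV/LVSV ratio below are assumptions, because the article gives none. A ratio near 1 is plausible because the Participants section excludes structural heart disease, including significant valvular disease. The range 0.90 to 1.10 was tested.

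**1. Size of the Qc error.** Let r = RVSV/LVSV.

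- Printed: (RVSV + LVSV/2) × HR
- Mean of ventricles: ((RVSV + LVSV)/2) × HR
- Ratio: (r + 0.5) / ((r + 1)/2) = (2r + 1)/(r + 1)

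| r | Printed / mean | Fick extraction (inverse) |
|---|---|---|
| 0.90 | 2.8/1.9 = 1.474 | 0.679 |
| 1.00 | 3.0/2.0 = 1.500 | 0.667 |
| 1.10 | 3.2/2.1 = 1.524 | 0.656 |

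Example with both stroke volumes 80 mL and HR 140: the mean form gives 80 × 140 = 11.2 L/min, and the printed form gives (80 + 40) × 140 = 16.8 L/min.

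**2. Change and fold.** Example with equal ventricles: rest SV 75 mL and HR 70; peak SV 85 mL and HR 140.

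| | Mean form | Printed form |
|---|---|---|
| Rest Qc (L/min) | 75 × 70 = 5.25 | 112.5 × 70 = 7.88 |
| Peak Qc (L/min) | 85 × 140 = 11.90 | 127.5 × 140 = 17.85 |
| Change (L/min) | 6.65 | 9.98 |
| Fold | 2.27 | 2.27 |

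The change is inflated by the same 1.5, given the same r at rest and peak. The fold does not move. If r shifts between rest and exercise within 0.90 to 1.10, the fold is multiplied by at most 1.524/1.474 = 1.034 and at least 1.474/1.524 = 0.967. Only women whose true fold lies between about 2/1.034 = 1.93 and 2/0.967 = 2.07 could then change class.

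**3. The regression for the prediction aim.** If printed Qc equals k times the mean form with k constant, the coefficient and its standard error are both divided by k. The test statistic, the fitted values and the discrimination are unchanged. Over the range tested, k departs from 1.5 by less than 2% (1.474/1.5 = 0.982; 1.524/1.5 = 1.016).

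**4. Unequal weighting.** With equal, independent errors in the two stroke volumes, the relative error is proportional to √2/2 = 0.707 for the mean and √(1 + 0.25)/1.5 = 0.745 for the printed form. The ratio is 0.745/0.707 = 1.05, a loss of precision of about 5%.

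**5. Memory score.** Take 8 words at trial 2, 12 at trial 5 and 12 after interference. The printed formula gives a loss of 12 − 8 = 4. Trial 5 minus the post-interference recall gives 12 − 12 = 0. Nothing was forgotten, yet a loss of 4 is recorded.

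**The case against.** The cardiac output line is very probably a misplaced bracket. The article says that images are analysed in in-house software and that the CMR method has been validated against invasive measures, so nothing shows that Qc is actually computed from the printed line. This stands: the error is conditional on someone following the text.

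A reader might infer that the prediction aim is compromised because its main predictor is 50% too high. The article does not support that, since a near-constant factor leaves the test and discrimination essentially as they were. The extra weight on the right ventricle costs only about 5% in precision. Oxygen extraction is not named in the outcome list.

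A reader might also infer that the predictor is left open, because peak Qc, change in Qc and a fold cut-off all appear. It is not: the Abstract and Background name peak exercise cardiac output, and the regression enters peak Qc. What remains is loose wording of cardiac reserve.

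A third inference is that the two-fold cut-off is misapplied, because the top stage is 60% of upright maximum power while "66% of the maximal power during upright cycling approximates maximal exercise capacity in a supine position". The cut-off comes from a cited source that is not visible here, and the stage at which it was derived cannot be checked. Any size for such a mismatch would also need an assumed shape for the rise in Qc.

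On memory, the article does not print the test layout, so calling trial 2 a learning trial is an assumption. The narrower point does not need it: the formula omits the post-interference recall. The score is one of several from one secondary test.

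**Conclusion.** Both formulas are wrong as printed and should be corrected.

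- **Qc, if followed literally:** absolute values and the change in L/min are about 50% too high (47% to 52% for RVSV/LVSV of 0.90 to 1.10, with the ratio the same at rest and peak for the change). Fick oxygen extraction is about 33% too low. The regression comparing peak Qc with LVEF and the two-fold classification are essentially unaffected, so neither primary aim is put at risk by this error.
- **Memory score:** it would measure something other than loss after interference and, with trials numbered in order, would count improvement as loss. This touches one secondary score and no sample-size figure.

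The Qc sizes rest on the assumed RVSV/LVSV range. The direction of the memory error rests on trial 5 following trial 2.

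**What to change.** 1. Print Qc = ((RVSV + LVSV)/2) × HR.
2. Define loss after interference as trial 5 minus the recall after interference.
3. Check that the imaging software and the analysis script use these forms, for example by recomputing Qc by hand from the stored volumes of a few participants.
4. Align the wording: state that peak Qc, measured at the high-intensity stage and already in the regression, is the predictor for the second primary aim, and that the change in Qc and the two-fold classification are supporting measures.

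The cost is a text edit and a short script check, with no change to the design or the planned model. Indexing Qc to body mass should not be part of this correction. The outcome is VO2peak per kilogram, so indexing would give predictor and outcome a shared denominator and change the comparison with LVEF.

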### Cardiac structure and function

#### Echocardiography

Resting RV and LV function will be assessed by a comprehensive resting echocardiogram (Vivid E95, General Electric Medical Systems, Milwaukee, Wisconsin) with images analysed using offline analysis software (Echopac v13.0.00, GE, Norway). Resting echocardiography represents the current clinical standard of care to which exCMR will be compared [15]. LVEF will be used as the primary ‘standard of care’ measurement, and will be quantified from a full-volume 3D dataset according to standard recommendations. Additional measurements performed will include Doppler, torsion, global longitudinal strain and strain rate measurements.

#### Cardiac magnetic resonance imaging

In addition to resting echocardiography, resting CMR (using the same protocol as described previously) [52] will be used to provide a highly accurate and comprehensive characterisation of resting cardiac structure and function. Breath-hold steady-state free precession (SSFP) sequences will be used for the quantification of ventricular volumes ventricular function and cardiac mass, whilst non-contrast T1 mapping will be used for myocardial tissue characterisation.

### Central vascular stiffness

Central (aortic) stiffness will be assessed using ECG-gated resting CMR cine-imaging conducted prior to the exCMR. Transverse images of the ascending aorta will be taken just above the sinotubular junction. Cine images will be analysed for changes in 2-dimensional area across the cardiac cycle that can be incorporated with SV (calculated from breath-hold SSFP images) and pulse pressure (obtained from brachial blood pressure measured by an automated cuff) to calculate aortic distensibility and compliance in line with previously validated methods [53].

### Biochemical and blood-based markers

Troponin-I and B-type natriuretic peptide (BNP) will be collected as markers of myocardial injury and myocardial stress respectively. These will be obtained from a non-fasted blood sample taken by a trained phlebotomist 10-min following the exCMR procedure. BNP will be analysed immediately at the Baker Heart and Diabetes Institute using a point of care analyser (Biosite [Alere] Triage MeterPro), whilst an additional sample will be sent immediately to the Alfred Hospital Pathology Laboratory for assessment of troponin-I and haemoglobin. Information related to the use of erythropoiesis stimulating agents or the occurrence of blood transfusion will be obtained from participant medical records. Participants will also have the option of providing ‘opt in’ consent for storing an additional 3.0 mL blood sample for result verification and future analysis of cancer and cardiometabolic-related outcomes.

### Blood pressure

Supine resting systolic- and diastolic BP and resting HR will be assessed from three measurements using an automated machine (OMRON HEM-907, OMRON Corporation, Tokyo, Japan). Measures will be collected after participants have been resting for at least 10-min, with at least 3 min in-between each measurement.

### Total and regional body composition and bone mineral density

#### Dual-energy X-ray absorptiometry

Total and regional fat mass, lean body mass and percentage body fat will be measured from a total body DXA scan (GE Lunar iDXA, GE Healthcare, Little Chalfont, United Kingdom) according to a standardised protocol. Regional composition will be manually assessed using enCore analysis software version 14.10.022 according to standardised procedures. DXA will also be used to quantify areal bone mineral density (g/cm^2^) of the total hip, femoral neck, and lumbar spine (L1-L4 vertebrae).

#### Magnetic resonance imaging

Muscle volume and muscle fat fraction of the quadriceps in the mid-thigh will be assessed by two-point Dixon-based MRI (Siemens Prisma 3 T MRI) conducted immediately prior to the CMR scans. The two-point Dixon method has been validated as an accurate and reproducible (CV = 0.6%) measurement of muscle-fat content [54, 55]. MRI scans of the dominant thigh will be acquired in the supine position, from the superior patella to the greater trochanter. Images will be transferred to a separate workstation for manual off-line analysis of thigh muscle volume and muscle fat fraction (ImageJ2 v1.52d). Muscle volume will be calculated from the summation of disks method by multiplying the sum of the combined regions of interest by the inter-slice distance. Fat fraction will be calculated from the ratio between the fat and combined fat and water signal intensities for the regions of interest.

### Anthropometry

Height and body mass will be used to calculate body mass index and body surface area. Waist circumference will be assessed at the mid-point between the iliac crest and lowest rib according to standard techniques [56].

### Muscle strength

Maximal isometric grip strength will be assessed using a digital grip strength dynamometer (Jamar Plus Digital, Lafayette Instrument Company, IN, USA) following a standardised protocol. Maximal dynamic muscle strength (in kilograms) of the upper body (seated row) and leg muscles (leg press) will be assessed on resistance machines using a 1RM protocol according to current guidelines [57].

### Physical function

Physical function will be assessed using the usual and fast gait speed test, 30-s sit-to-stand test, and timed stair climb. All tests will be performed in triplicate, with the best of the three scores used for analysis.

#### Timed stair climb

The timed stair climb test is a measurement of lower limb muscle power [58]. Participants will be instructed to climb one flight of 12 stairs (17 cm per step) as quickly and safely as possible, using the handrail only if necessary for safety purposes or to regain balance. Stair climb power will be calculated according to the following formula:
$$ \left[\mathrm{weight}\ \left(\mathrm{kg}\right)\mathrm{x}\;9.81\ \mathrm{x}\ \mathrm{step}\ \mathrm{height}\ \left(\mathrm{m}\right)\ \mathrm{x}\ \mathrm{step}\ \mathrm{number}\right]\div \mathrm{time}\ \left(\sec \right) $$

#### Sit to stand test

The 30-s sit to stand test will be used as a measurement of functional lower limb muscle endurance [59]. Participants begin in a seated position (on a chair of standardised height) with their arms folded across their chest. When instructed by the researcher, participants are required to stand fully upright and return to a seated position as many times as they can in 30 s.

#### Gait speed test

The usual- and fast- pace gait speed test is a measure of gait speed and functional mobility [60, 61]. For the usual gait speed test, participants will be required to walk at their usual walking speed between two cones spaced eight metres apart (consisting of a 2 metre acceleration zone, a 4 metre timed zone, and a 2 metre deceleration zone). The time begins when the participant’s front foot enters the timed zone and ends when their front foot enters the deceleration zone. The fast gait speed test is performed in an identical fashion, however in this instance participants are instructed to cover the distance as quickly and safely as possible without running.

### Cognitive function

A series of short verbal and paper-based tests will be used to assess different domains of cognitive function that may be negatively impacted during chemotherapy, including verbal memory, short-term and working memory, and executive function [62].

#### Rey auditory verbal learning test

Changes in verbal memory and learning will be assessed using the Rey Auditory Verbal Learning Test [63]. Outcomes include the total number of words correctly recalled on each attempt, the number correctly recalled after interference, loss after interference (trial 5 minus trial 2) and correct recall after the extended delay period.

#### Digit span test

Short-term and working memory will be assessed using the Digit Span Test [64]. Changes in short-term memory will be assessed using the forwards digit span test and working memory will be assessed using the reverse digit span test. Participants will be scored on the number of sequences recalled correctly for each condition.

#### Trail making test

Changes in executive function will be assessed using the Trail Making Test (Parts A and B) [65].

#### National Adult Reading Test

*The* National Adult Reading Test will be administered to assess verbal, performance and full-scale intelligence quotas as an estimate of premorbid intelligence [66]. Participants are scored based on the number of pronunciation errors. As this test is a measure of premorbid intelligence it will only be administered at baseline.

### Health-related quality of life, fatigue and mood

Health-related quality of life and fatigue will be assessed by the Functional Assessment of Cancer Therapy-Breast (FACT-B) and Functional Assessment of Cancer Therapy-Fatigue (FACT-F) questionnaires respectively, whilst mood will be assessed using the Hospital Anxiety and Depression Scale. All of these questionnaires have been validated for use in cancer patients [67–69].

